## Background

Convergence insufficiency (CI) is a binocular vision problem characterized by an excess of exophoria in near activities compared to distance, moreover, its includes remoted near point of convergence (NPC) and decreased positive fusional vergence (PFV) [1]. Its prevalence typically ranges from 2.25 to 17.6%, depending on the population studied and the criteria used to define it [2–5]. This problem is also frequently observed in individuals with presbyopia with prevalence of 29.6% [4]. The most common ocular finding in these patients is an increase in near exophoria, which can impair performance in activities such as reading, computer work, and other near tasks [6]. Symptoms of CI include difficulty seeing at close range, headaches, eye pain during reading or studying, blurred vision, diplopia, movement of words while reading, a feeling of pressure in the eyes, and difficulty concentrating. Signs of it include an increasing near point of convergence, more exophoria at near than distance, a decreased AC/A ratio, and a decreased positive fusional vergence [7] and the convergence insufficiency symptom survey (CISS) questionnaire is the initial standardized and valid tool used to evaluate the frequency and nature of symptoms in patients with CI [8, 9]. Vision therapy is typically considered as the primary treatment option for CI, with base in prism prescription being an alternative choice [6]. However, given the age-related changes in the interaction and functioning of the accommodation and convergence systems, it is crucial to study how these systems interact in elderly individuals [7]. It is also important to compare the responses of these age groups to vision therapy and base in prism prescription [10]. While vision therapy has proven effective in reducing symptoms and enhancing visual function in patients with CI, the different accommodation and vergence systems in elderly individuals may yield different results [11]. There is little information about CI in presbyopic subjects, to our knowledge, in these patients, only one study investigated vision therapy [12] and base in prism prescription in which prism proved superior albeit in a very small sample of participants [13].; also patients age can impact the vision therapy compliance [14] and the documentation of effectiveness of vision therapy and base in prism prescription in presbyopic individuals with convergence insufficiency is insufficient.

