#### Sample size calculation

To calculate the appropriate sample size for all outcome variables specially those related to primary outcomes, a two-tailed test with α = 5% and β = 10% and 90% power was conducted using the Power Analysis & Sample Size software (PASS, version 11). The selection of appropriate statistics for the sample size determination was based on three previous studies [10, 12, 13]. The sample size in each group was determined using the One-way ANOVA menu of PASS 21 software, taking into account the quantitative nature of the dependent variables and the presence of three groups. The test was conducted with a first type error (α) of 0.05 and a second type error (β) of 0.1, corresponding to a test power of 90%. The mean values of 17 cm, 16 cm, and 21.52 cm, along with a standard deviation of 7.50, were extracted for NPC, and the effect size was calculated as 0.311. Considering a 15% dropout rate, the total number of samples in each group amounted to 50, resulting in a combined total of 150 samples.

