
To ensure that the optometrist conducting the clinical testing remains unaware of the prism near spectacles, in follow up visits, all glasses will be examined in a separate unit by another optometrist and [name] will not investigate the new habitual spectacles.

To ensure and encourage adherence, a written log detailing the daily usage of near spectacles, including approximate durations and descriptions of home exercises, will be maintained. In addition, video calls will be conducted to monitor and promote compliance. Participants are strongly encouraged to remain engaged in the study. Individuals who have successfully finished the study will receive the spectacle prescription at no cost. In the event that a participant is unable to continue or cooperate, they will be replaced by another individual.

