#### Statistical methods

Analysis will undergo using the Statistical Package for the Social Sciences software (SPSS version, 22). The significance levels of α and β will be set at 5% and 10%, respectively, while the confidence interval will be established at 95%. To compare the research variables before and after the intervention, the paired t-test or its non-parametric equivalent will be utilized. The normality of the data will be checked using the Kolmogorov- Smirnov test. One-way ANOVA with Tukey’s post hoc test will be employed to compare the quantitative variables in the study. ANCOVA will be used to eliminate any intervening variables. The Kruskal-Wallis and Mann-Whitney tests will be used to evaluate groups of quantitative variables in non-parametric conditions. For within-group analysis, repeated measures ANOVA will be conducted when initial homogeneity and normality of data are met. If initial homogeneity is established without normality of data distribution, the Friedman test will be used. A linear mixed model adjusted for the baseline variables will be employed when initial homogeneity is not found. Per protocol analysis principles will be applied in the study. Additionally, univariate analysis and multiple regression analysis will be conducted to identify the predictor factors that influence prism effectiveness in presbyopic patients.

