Ensuring compliance is crucial for the effectiveness of home vision therapy treatment. Consequently, this study also seeks to evaluate the level of compliance among patients undergoing each treatment approach. Additionally, the study aims to investigate the potential occurrence of adverse effects associated with vision therapy or base in prism prescription. It has been hypothesized that there might be a theoretical risk of adverse events such as nausea, headache, diplopia, and prism adaptation. However, previous studies have not reported any instances of these events.

The implementation of masking procedures guarantees that clinical assessments are conducted in a manner that eliminates bias. Consequently, the treating optometrist will have no access to assessment results, either through the database or medical notes. Furthermore, strict controls are in place to prevent the treating optometrist from providing further treatment to the participants after the study, thereby ensuring that they cannot obtain the resultant binocular measurements.

The focus of this study is dedicated to patients aged 40 years and above. Birnbaum et al. [12] conducted a study involving patients aged over 40 years, which resulted in lower functional cure rate in home-based vision therapy than office-based vision therapy. This improvement was observed in terms of near point of convergence and positive fusional vergence development. In presbyopic patients with CI Wick [26] expressed that 10–15 weeks of home vision therapy can improve stereopsis and near point of convergence in 92% of patients. In a retrospective study by Westman et al. [27] in patients with age of 6–79 years of old ages office based vision therapy caused 37% improvement in near point of convergence and near positive fusional vergence. Also the findings of Teitelbaum et al. [13] demonstrated enhancements in individuals with convergence insufficiency (CI) who were also presbyopic, achieved through the application of progressive additional lenses with base in prism. Therefore, it is plausible that similar improvements could be attained in older patients utilizing base in prism prescription and vision therapy. However, presently there are no formal plans to evaluate this specific aspect, as the primary objective is to establish an optimal treatment protocol for individuals with CI who are also presbyopic.

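### Per protocol is the only stated analysis principle and non-cooperating participants are replaced, so the comparisons between arms lose the protection of randomisation

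*Protocol article*

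**What the plan says.** Statistical methods (protocol article) fixes the analysis principle in one sentence: "Per protocol analysis principles will be applied in the study". The article mentions no intention-to-treat analysis, no full analysis set and no sensitivity analysis on everyone randomised. It does not define the per-protocol set or give an adherence threshold.

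Data collection adds a second rule: "In the event that a participant is unable to continue or cooperate, they will be replaced by another individual". The sample size already allows for losses: "Considering a 15% dropout rate, the total number of samples in each group amounted to 50, resulting in a combined total of 150 samples".

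The objectives list three pairwise comparisons, each meant to tell arms apart, and the Discussion looks for differences between arms in order to choose a treatment strategy. On adherence, the Background remarks that "also patients age can impact the vision therapy compliance" and the Discussion that "Ensuring compliance is crucial for the effectiveness of home vision therapy treatment".

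Statistical methods does mention a baseline-adjusted linear mixed model, but only for the case where the groups are not homogeneous at the start.

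**The concern.** Randomisation makes the arms comparable at allocation. A per-protocol set is chosen afterwards, by behaviour that may depend on the assigned treatment and may be related to prognosis. The groups finally compared are then not those that randomisation formed, and the nominal 5% error rate is no longer assured. Replacement adds to this by substituting different people for those who did not cooperate.

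There are reasons to think exclusion could differ by arm. Home therapy involves a repertoire of eight convergence and accommodation exercises, four per session, 20 minutes three times a week for two months. The other two arms do placebo eye movements at 6 m. A form for recording exercise duration is described specifically for the therapy arm, so lapses in exercise may be noticed more readily there. The question the trial wants to answer, which treatment to prescribe, would be replaced by a comparison of those who complied.

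**Working it through.** **1. The plan's own sample size.** Inputs from Sample size calculation: "The mean values of 17 cm, 16 cm, and 21.52 cm, along with a standard deviation of 7.50, were extracted for NPC", α 0.05, power 90%, three groups.

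- Mean of the three means: 18.173. Squared deviations: 1.377 + 4.723 + 11.200 = 17.300.
- f = √(17.300/3)/7.5 = 2.401/7.5 = 0.320 (the article states 0.311).
- One-way ANOVA, noncentral F: 43 per group (power 90.6%). 43/0.85 = 50.6, so 51; 43 × 1.15 = 49.5, so 50.

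The planned 50 per group therefore reproduces to within one patient, and it already includes the 15% allowance (0.15 × 150 = 22.5 patients). Replacement is not needed to protect the planned number.

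**2. What exclusion can do when there is no true effect.** The article gives no adherence by arm and no link between adherence and outcome, so these are assumptions. Let p_v and p_c be the fractions excluded in the therapy and comparator arms. Assume that anyone who would be excluded in the arm with fewer exclusions would also be excluded in the other. Let those excluded in the arm with more exclusions have a prognosis g SD worse than those retained there. For p_v ≥ p_c, the retained comparator group still contains a fraction (p_v − p_c)/(1 − p_c) of such patients, so

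- bias b = g × 7.5 × (p_v − p_c)/(1 − p_c), positive when it favours therapy;
- SE = 7.5 × √[1/(50(1 − p_v)) + 1/(50(1 − p_c))];
- type I error = Φ(−1.96 + b/SE) + Φ(−1.96 − b/SE), for one pairwise comparison.

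Central case, 25% against 5%, g = 0.5: b = 0.5 × 7.5 × 0.20/0.95 = 0.79 cm; SE = 7.5 × √(1/37.5 + 1/47.5) = 1.64; type I error 7.7%.

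| Excluded, therapy / comparator | g | Bias (cm) | Type I error |
|---|---|---|---|
| 15% / 15% | any | 0 | 5.0% |
| 15% / 5% | 0.25 | 0.20 | 5.2% |
| 25% / 5% | 0.50 | 0.79 | 7.7% |
| 30% / 5% | 0.75 | 1.48 | 14.4% |
| 5% / 15% (roles swapped) | 0.50 | −0.39 | 5.7% |

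For gaps of 0.25 to 0.75 SD and exclusions of 15–30% against 5–15%, the range is 0 to 1.5 cm and 5% to 14%.

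**3. Check under a different model.** A simulation (4,000 trials per setting, 50 per arm, SD 7.5, no true effect) made exclusion depend on a latent adherence score correlated with improvement. With 30% against 5% excluded, the bias was +0.9 cm (type I error 7.9%) at correlation 0.3 and +1.5 cm (14.9%) at 0.5. It was about 0 at correlation 0 and −0.9 cm at correlation −0.3, where good responders stop. With 5% against 15% it was −0.4 to −0.7 cm at correlations 0.3 to 0.5. Analysing everyone as randomised stayed near 0 cm and 5% throughout, given complete outcome data.

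**4. Cost in power of analysing everyone.** Assume that 21.52 cm is the control mean and that non-adherers in both active arms gain nothing, so f shrinks in proportion. With all 50 per arm analysed:

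- no non-adherence: f = 0.320, power 94%;
- 15% non-adherence: f = 0.85 × 0.320 = 0.272, power 85% (58 analysed per arm needed for 90%);
- 30% non-adherence: f = 0.70 × 0.320 = 0.224, power 68% (85 needed).

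**The case against.** A reader might infer that the plan biases the result in favour of home therapy. The document does not support that. The per-protocol set is undefined, so it may exclude low adherers or only non-completers. Adherence by arm is not reported. All arms have home exercises, spectacles to wear, logs and video calls. The dose of the placebo exercise is not stated, so the relative time burden is unknown. The prism arm may have its own reasons to stop, since the Safety assessment names nausea, headache and diplopia as conceivable events. The Background says only that age may affect compliance, and age is a factor in the randomisation. This objection stands: direction and size are assumptions.

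The size also needs context. The central 0.8 cm is a fifth of the 4 cm that the objectives call clinically significant for NPC, and 1.5 cm is 37% of it. The 15% dropout allowance is not a count of per-protocol exclusions, and dropouts without outcomes are a missing-data problem under any principle.

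It could further be said that a separate analysis plan may define an all-randomised analysis, or that the objectives speak of efficacy. Neither removes the point. The article does not leave the principle open but chooses one, and an analysis plan using all randomised participants would contradict it. An efficacy aim does not make groups selected after randomisation comparable.

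**Conclusion.** The point holds as a defect of a stated rule. For a three-arm trial meant to show differences, per protocol is the only principle given, and the replacement rule compounds it. Both can bias the between-group comparisons. The defect does not depend on which way the bias runs.

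The illustrated 0 to 1.5 cm and 5% to 14% rest on assumed exclusion rates, an assumed prognosis gap and nested exclusion. They show what could happen, not what will. The article reports 121 patients randomised by 3 October 2023, so the text can be corrected before the analysis and the remaining follow-up protected, but outcomes already lost may not be recoverable.

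**What to change.** In Statistical methods, replace the per-protocol sentence with wording such as:

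> The primary analysis includes all randomised participants in the group to which they were assigned, whatever their adherence. Participants who do not adhere are still measured at 1 and 2 months. The primary between-group comparison uses the baseline-adjusted linear mixed model in all cases, and missing visits are handled within it. A per-protocol set, defined before the analysis, serves as a sensitivity analysis.

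The condition that reserves the mixed model for non-homogeneous baselines must be removed for the primary comparison; otherwise the two statements conflict. Measuring non-adherers matters because a participant with no follow-up visit contributes nothing to a model adjusted for baseline.

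In Data collection, delete the replacement rule, as the 15% allowance already covers losses. Anyone already replaced stays in the analysis as randomised, with whatever data exist.

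The cost is a short amendment and continued follow-up visits for non-adherers. The estimated effect and the power may fall: to about 85% if 15% of both active arms are non-adherent and gain nothing, and to 68% at 30%. The protocol should state this; it is not a reason to exclude patients.

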#### Eligibility criteria

For inclusion in the study, participants must meet the following criteria: a CISS score exceeding the cut-off point established in phase 1 using our modified CISS, near and far best corrected visual acuity of 20/20, presence of CI, near exophoria being at least 4 prism diopters greater than distant exophoria, near point of convergence greater than 6 cm, inadequate near-positive fusion as defined by the Convergence Insufficiency Treatment Trial (CITT) study [17], and normal monocular accommodation amplitude as per the Hofstetter formula.

Participants will be excluded from the study if they meet any of the following criteria: dry eye, any form of strabismus or amblyopia, spherical refractive error ≥ 3.50 diopters, astigmatism ≥ 2.50 diopters, history of prism prescription, vision therapy undergone less than five years ago, history of strabismus or refractive error surgery, history of eye trauma, use of any ophthalmic or general medications or drugs that affect ocular accommodation, such as phenylephrine, anticholinergics (mydriatics), carbonic anhydrase inhibitors, antihistamines, morphine and its derivatives, antidepressants, amphetamine, and imipramine, presence of more than one prism of vertical phoria, any mechanical limitations in the eye muscles, ocular muscle paralysis, nystagmus, and any systemic or neurological diseases that affect binocular vision, such as diabetes, myasthenia gravis, Graves’ disease, and multiple sclerosis.

To ensure blinding, participants will be kept unaware of which group they have been assigned to. Those who express interest in participating in the study and meet the eligibility criteria will be asked to sign an informed consent form. The optometrist responsible for recruitment, [name], will carry out the preliminary evaluation after the participant’s score in the modified CISS questionnaire has been determined.

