#### Prism prescription group procedure

The prism prescription group will be given the same treatment protocol and instructions as the control group. However, near prismatic glasses will be prescribed using the Sheard’s criterion and their appropriated addition power, and the base in prism will be rounded up and evenly distributed between both eyes. Sheard’s criterion is most popular guideline for prism prescription and it demonstrates optimal effectiveness when applied to individuals with exophoric conditions [18]. They will also be instructed to perform random and aimless eye movements, of which will be done at a distance of 6 m and over a 2 cm area, as mentioned previously they will not affect the convergence and accommodation system.

In all groups, if participants have a refractive error for distance vision, they will be provided with two separate pairs of spectacles, one for near use and one for distance use. To ensure regular usage of the near spectacles (with or without prism) throughout the study, adherence will be monitored through video calls and by participants confirming their usage on an instruction form.

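### The regression planned to find what influences prism effectiveness states no control comparison and no arm-by-factor interaction, so it would find who improves, not in whom prism helps more than control

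*Protocol article*

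**What the plan says.** After the between-group and within-group tests, the Statistical methods section adds one further analysis: "univariate analysis and multiple regression analysis will be conducted to identify the predictor factors that influence prism effectiveness in presbyopic patients". The sentence gives an aim and a method. It does not name the response variable, the arms included, the candidate factors or any interaction term, and no other section supplies them for this analysis.

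Three other parts of the article bear on it:

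- **A comparator exists.** Under Prism prescription group procedure, "The prism prescription group will be given the same treatment protocol and instructions as the control group", with prism added to the near glasses. Control participants also receive new near glasses and placebo eye movements.
- **Entry selects on outcome measures.** Eligibility criteria require "a CISS score exceeding the cut-off point established in phase 1 using our modified CISS", "near point of convergence greater than 6 cm" and inadequate near positive fusion. The Outcomes section lists NPC and near PFV as primary and CISS as secondary.
- **Arm size.** Under Sample size calculation, "Considering a 15% dropout rate, the total number of samples in each group amounted to 50".

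**The concern.** In a randomised trial the effectiveness of prism is the prism-minus-control difference. A factor influences it only if that difference changes with the factor, which is an arm-by-factor interaction. A regression of patients' results on factors estimates something else: the association between the factor and the result.

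Two things produce such associations when nothing modifies the prism effect. The first is prognosis: some patients do better whichever glasses they are given, and all three arms receive new near glasses. The second is regression to the mean: patients are admitted because NPC, PFV and CISS are abnormal, so the more extreme baselines tend to move back in every arm. A pooled regression without an interaction does not remove either.

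The Discussion sets the trial up to test, under controlled conditions, improvements seen in uncontrolled studies. A predictor analysis without a control contrast goes back to uncontrolled inference. The risk is a published list of predictors of prism effectiveness that carries no information about the benefit of prism over control.

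**Working it through.** **Arm size.** The article gives no figure for the predictor analysis, so the only plan figure needed is the number per arm. The design is "a two-tailed test with α = 5% and β = 10% and 90% power was conducted" in a three-group one-way ANOVA, and "The mean values of 17 cm, 16 cm, and 21.52 cm, along with a standard deviation of 7.50, were extracted for NPC".

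- Mean of the three values: (17 + 16 + 21.52)/3 = 18.173.
- Squared deviations: 1.377 + 4.723 + 11.200 = 17.300. SD of the means = √(17.300/3) = 2.401.
- f = 2.401/7.50 = 0.320. The article says "the effect size was calculated as 0.311", a small mismatch that does not matter here.
- With f = 0.320, the noncentral F gives 43 per group (power 0.906).
- Dropout: 43/0.85 = 50.6, so 51; or 43 × 1.15 = 49.45, so 50. The stated 50 is reproduced within one patient.
- Evaluable per arm after 15% dropout: 50 × 0.85 = 42.5, taken as 42.

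**Case 1: a purely prognostic factor, prism arm only.** The factor correlates r with the result equally in every arm, so the true interaction is zero. The values of r are assumptions. By Fisher's z, the chance of p < 0.05 is about Φ(atanh(r) × √(n − 3) − 1.96), with n = 42 and √39 = 6.245.

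| r | atanh(r) | × 6.245 | Closed form | Simulation (20,000 trials) |
|---|---|---|---|---|
| 0.3 | 0.310 | 1.933 | 0.49 | 0.50 |
| 0.4 | 0.424 | 2.646 | 0.75 | 0.76 |
| 0.5 | 0.549 | 3.430 | 0.93 | 0.94 |

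In the same simulation an arm-by-factor interaction test was significant in about 5% of trials.

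**Case 2: prism and control pooled, arm as a main effect, no interaction.** Now n = 84 with one covariate, so the multiplier is √(84 − 1 − 3) = 8.944. For r = 0.3, 0.310 × 8.944 = 2.768 gives 0.79; for r = 0.4, 0.424 × 8.944 = 3.789 gives 0.97. Pooling makes the false attribution more likely, because the larger sample detects the prognostic association more easily.

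**Case 3: baseline severity, if the response is a change score.** With no effect and equal variances, baseline correlates with improvement at √((1 − ρ)/2), where ρ is the baseline-to-follow-up correlation (assumed).

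- ρ = 0.5: √0.25 = 0.50. Flagged in about 93% (simulation 94%).
- ρ = 0.8: √0.10 = 0.316, and 0.3275 × 6.245 = 2.045. Flagged in about 53% (simulation 54%).

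**Second simulation, different assumptions.** 2,000 runs per setting, 42 or 50 per arm, assumed measurement reliability 0.6 to 0.9, no effect modification:

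| Test | Flagged at p < 0.05 |
|---|---|
| Baseline against change, prism arm, single factor | 22% to 87% |
| Baseline against change, prism arm, multiple regression | 30% to 90% |
| Prognostic factor (0.3 SD per SD), prism arm | 63% to 99% |
| Prism-by-factor interaction against control | 4% to 6% |

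**Power of the interaction test.** The slope difference detectable with 80% power is about (1.960 + 0.842) × √(2/n) outcome SD per SD of the factor: 2.802 × √(2/42) = 0.61, or 2.802 × √(2/50) = 0.56.

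**The case against.** The strongest reply is that this is one condensed sentence in a journal article, and that the response, arms, factors and model terms of an additional analysis are commonly left to the full protocol or analysis plan. A multiple regression can contain an interaction. This stands in part: silence on those details is no fault in itself. What remains is that the article pairs an aim with a method, and the method as written does not answer the aim. A univariate analysis cannot hold an interaction, and none is stated for the multiple regression.

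A reader might infer more than the text supports:

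- **That factors are screened univariately before the multiple model.** The article names both analyses but describes no screening step. With ten unrelated factors tested at 5%, 1 − 0.95^10 = 0.40, but ten independent interaction tests carry the same 40%. That figure argues for a short list of factors, not for interactions.
- **That the response is a change score.** It is not named. Case 3 applies only if it is, and the same section mentions ANCOVA and baseline-adjusted models elsewhere. Truncation of baseline at entry could also lower those percentages.
- **That the model is confined to the prism arm.** This is not stated. Case 2 shows that pooling without an interaction does not cure the problem.
- **That the trial's main conclusions are at risk.** They are not. This analysis is additional to the stated objectives and outcomes.

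It is also fair to say that the percentages in Case 1 are the power to detect a real prognostic association. They become error rates only when the finding is reported as an influence on prism effectiveness, which is how the article words it.

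**Conclusion.** The concern holds in a limited form. As written, the analysis would identify factors associated with improvement, and they would be reported as factors that influence the effectiveness of prism. With about 42 evaluable patients per arm and assumed correlations of 0.3 to 0.5, a purely prognostic factor would be flagged in roughly 50% to 94% of trials by a prism-arm regression, against about 5% by an interaction test. If a change score is used, baseline severity would also be flagged far above 5%. The direction holds across every setting tried. The exact sizes rest on correlations and reliabilities that the article does not give. The three between-arm comparisons and the sample size are unaffected, so this is a worthwhile correction to an additional analysis and not a threat to the trial.

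**What to change.** Replace the sentence with one on these lines: modification of the prism effect will be explored in a baseline-adjusted model of prism and control participants, with arm-by-factor interactions for a few factors named in advance (for example age, baseline near exophoria, baseline NPC and baseline PFV). Interaction estimates will be given with 95% CIs, and the analysis will be labelled exploratory.

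If the regression is kept as it is, describe its results only as predictors of outcome among prism wearers, and drop the reference to prism effectiveness. That also means stating that it is fitted in the prism arm.

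The cost is a few lines of analysis code and no new data. The downside is power: only a slope difference of about 0.56 to 0.61 outcome SD per SD of the factor would be found with 80% power, so fewer predictors will be reported and a null interaction will not rule out moderate modification.
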